### Cellphone use in Cambodia

Cambodia is the first country in the world where the number of mobile phone users has surpassed the number of fixed landlines [40]. The number of mobile subscribers in Cambodia reached 20 million at the end of 2013, surpassing the country’s population by about five million [41]. In a survey of 2597 youth aged 15–24 years drawn from all 24 provinces in Cambodia, 96% declared that they had access to a phone, with 68% reporting that they owned a personal mobile phone, and 72% had a mobile in their home [42]. The percentage of Cambodian people who own at least one smartphone was 39.5% in 2015, almost doubling the 2013 figure [43]. Controlling for location and gender, 51.3% of people aged 15–65 years in 2015 had at least one phone through which it was possible to send and receive messages in Khmer script (a 65% increase from last year) [44].

In a recent report from the United Nations Development Program (UNDP), of 2597 Cambodian people aged 15–24 years, 98% reported that they used their mobile phones mostly for making and receiving calls, 43% for listening to the radio or music, and 32% for sending and receiving messages, followed relatively closely by playing and downloading games (27%) and taking photos (22%) [42]. Of those youth who used SMS, the majority used English-language messages (81%) [42]. In the Asian-Pacific countries, the number of mobile social media users was set to reach one billion by the fourth quarter of 2015; and in Cambodia, increasing 108% from the previous year [45]. According to our recent observation study, FEWs have both smart and basic mobile phones, use them daily to text and engage in social media, and have expressed interest in receiving health information through their phones [46].

### Goal and objectives

The overall goal of the study is to deploy and rigorously evaluate the efficacy of the *Mobile Link*, an innovative intervention to engage young FEWs in Cambodia through frequent SMS/VMs that link them to existing high-quality HIV, SRH, and other related services. Specific objectives include: (1) developing the *Mobile Link*, a 12-month, two-arm randomized controlled trial (RCT), by conducting participant observation, focus group discussions (FGDs), in-depth interviews (IDIs), and revision workshops to produce a bank of theory-informed SMS/VMs as well as pilot testing the feasibility of collecting data from FEWs through SMS and VMs; (2) evaluating the efficacy of the *Mobile Link* at the individual and venue level in improving HIV and SRH behaviors and increasing the uptake of comprehensive HIV, SRH, and other related care services among sexually active FEWs; and (3) determining the cost-effectiveness of the *Mobile Link* for FEWs as compared to KHANA’s standard outreach, care, and treatment services.

## Methods

This manuscript is in accordance with the Standard Protocol Items: Recommended items to address in a clinical trial protocol and related documents (SPIRIT) guidelines (see Additional file 1 for SPIRIT checklist).

### Study design

The *Mobile Link* is a multisite, single-blind, 12-month RCT with two arms of 300 FEWs each (see Fig. 1). The trial will be conducted in the capital city of Phnom Penh and three provinces with high burden of HIV and a large proportion of FEWs including Battambang, Banteay Meanchey, and Siem Reap. The intervention would be developed following a review of the literature, formative research including surveys, interviews, and observations of FEWs, with inputs from public health professionals and technology partners in Cambodia. The *Mobile Link* conceptual framework (see Fig. 2) is based on the existing literature of the determinants of risk behaviors (i.e. unprotected sex) and utilization rates of prevention and treatment services (i.e. HIV and STI testing and treatment, contraceptive use).

**Fig. 1 Fig1:**
[figure not shown]
Study flow *diagram*

**Fig. 2 Fig2:**
[figure not shown]
*Mobile Link* intervention logic model

### Participant selection criteria

All participants must: (1) work at an entertainment venue in the selected study sites; (2) be currently sexually active defined as having engaged in oral, vaginal, or anal sex in the past three months; (3) own a mobile phone; (4) know how to retrieve VM or retrieve and read SMS on a mobile phone (Khmer or Romanized Khmer); (5) self-identify as a FEW; (6) be willing to receive two SMS/VM per week for one year; (7) provide a written informed consent; and (8) agree to a follow-up visit after six months and 12 months. Figure 1 depicts participant flow diagram for the study.

### Theory of change

The logic model (Fig. 2) illustrates how the *Mobile Link* seeks to meet the goal of reducing the incidences of HIV, STIs, unintended pregnancies, and gender-based violence (GBV) among FEWs in Cambodia. It presents the flow of inputs and activities that are expected to lead to the stated short-, medium-, and long-term outcomes for the FEWs served. The first column of the logic model describes the inputs, including KHANA staff, faculty from Touro University California, funders, technology partnerships, skills, KHANA’s implementing partners, and HIV information sources that support program delivery. The activities include ethical approval, staff hiring, participant surveys, staff training, FGDs/IDIs, qualitative data analyses, message creation, message pre-testing, platform creation, questionnaire administration and data analyses (at baseline, midline, and endline), and message service delivery. Collectively, these make up the outputs. This output translates into short-, medium-, and long-term outcomes/impacts. Outputs offer knowledge. Ideally, this knowledge is of the services, existing resources, SRH, and risks within relationships. The positive attitudes toward SRH, SRH resources, risks within relationships and condom use, and negotiation, along with the knowledge will promote skill acquisition and positive behavior change including increased HIV and STI screening and treatment, consistent condom use with clients and/or boyfriends, contraception use, abortion, and experiences with GBV. In addition, lower experiences of STI symptoms, received STI diagnosis, self-reported HIV status should occur with higher utilization of peer counselors and utilization of any other services of KHANA's implementing partners. All of the knowledge, attitudes, skills, and behaviors will culminate in the impact/long-term outcomes of the program.

### Sampling and participant recruitment

We will use a stratified random sampling method to recruit survey participants. Venues will be selected from a list of all entertainment venues in the study sites based on a recent report on geographic information system (GIS) mapping of HIV key populations in Cambodia [47]. They are matched with 30 similar venues and then randomized for size and type of the venues. We will continue to sample from our list of all entertainment venues until we have a total of 600 FEWs recruited. All enrolled participants will complete an informed consent and a baseline questionnaire survey. Next, one venue from each venue pair will be randomly assigned to the intervention group: VM or SMS (1) and the other to the control group (0) with standard of care (no additional mobile phone-based SRH support) with a 1:1 venue allocation ratio. Both groups will be followed for one year, and a six-month and 12-month questionnaire will be administered by trained data collectors (see Fig. 3).

**Fig. 3 Fig3:**
[figure not shown]
SPIRIT figure for *Mobile Link* protocol

When approaching participants, recruiters will explain the details of the study and ask them for their informed consent to participate and enroll them in the study. If they agree, they will be asked questions regarding the inclusion/exclusion criteria. The community health workers will provide a list of all participants recruited, together with a unique trial identification number, to the program coordinator delivering the intervention. The community health workers will send only the ID number together with type of the entertainment venue of enrolled participants to the project statistician via email. Allocation will therefore be concealed from the researchers working on the trial. The enrollment procedures will also require them to give mobile numbers for all of their SIM cards, as many people in Cambodia have multiple SIM cards. We will also ask them which phone number is their most used one.

### Baseline data collection

All data collectors and field supervisors will attend a training session for two days covering necessary skills including interview techniques, confidentiality, and privacy assurance. The study protocol and tools will also be reviewed during the training sessions in order for the team members to be thoroughly familiar with it. We will also include quality control skills such as rechecking and reviewing the questionnaires after administration as well as resolving issues that might arise during the fieldwork. Team leaders will be encouraged to perform regular review sessions with interviewers during the survey period to review progress and communicate any issues occurring during the data collection.

Given the high rates of illiteracy in this community, the data collectors will verbally explain the study by reading the participant information provided as part of the informed consent process before starting FGDs and interviews. If a FEW wishes to participate, she would express her verbal consent (see Additional files 2 and 3). In addition, a witness that is not associated with the study will be present and will sign the informed consent form.

Data collectors, who will be blinded to the trial arm assignment, will collect baseline data from participants recruited, as well as survey them at six and 12 months. All participants will receive SMS/VM appointment reminders for the surveys and peer data collectors will meet participants in a convenient and private location to conduct the surveys. If a participant misses a scheduled study visit, data collectors will send SMS/VMs and make voice calls to re-schedule the missed visits. If unsuccessful in contacting the participant through those modes, they will arrive in person at the workplace in an attempt to follow-up with the participant.

### Intervention

#### Phase I: Iterative, participatory intervention development

In phase 1, a total of 27 FGDs were conducted across all four implementation sites and among all four entertainment venue types, including street-based and on-call sex workers (for FGD guides see Additional file 4). IDIs were held with program staff as well as with FEWs living with HIV. The FGD guides were semi-structured and explored a range of topics related to HIV, SRH, GBV, and substance use. Conversation and storytelling were encouraged. Recognizing potential variable experiences and needs across entertainment venue types and geographic areas, FGDs were conducted across venue types among all four sites to achieve saturation.

Following initial data analyses, messages have been created with a local NGO, Women’s Media Center, and presented to a selected group of FGD participants and outreach workers to revise and refine messaging. The findings from the FGDs and revision workshops highlighted that for many FEWs, health priorities such as adverse effects of high alcohol use (gastrointestinal issues) and gynecologic issues (STIs and vaginal infection/irritation) outweigh concerns around HIV and family planning. In fact, during the revision workshops, HIV was most often cited as an area that women did feel they had a good knowledge base and linkage to testing and treatment. Participants also reinforced through discussions a number of misconceptions related to contraception – particularly oral contraceptives and intrauterine devices (IUDs) – as well as HIV and STI transmission. Many of those misconceptions will be directly addressed through the *Mobile Link* messaging. Lastly, many participants spoke to the importance of outreach workers and the linkages that Smart Girl provides, further confirming the emphasis on *Link* within the *Mobile Link* program.

Based on the formative research, messages tagged within the following topic areas (acknowledging some crossover) will be sent to intervention participants: gynecologic health; condom use; HIV; STIs; contraception; substance use; violence; infertility; cancer; and pregnancy. Further and more detailed findings from the formative phase are in the process of being synthesized for dissemination. Using the message bank, the SMS/VM platform and tracking will be developed and optimized for program use in collaboration with local programmers at the InSTEDD iLab in Phnom Penh.

#### Phase II: Intervention

The *Mobile Link* intervention comprises a series of automated SMS/VMs to participants’ mobile phones over the 12-month period. Participants will receive the first message within the first day of the intervention. The messages will be designed to enhance and increase utilization of existing HIV and SRH services by reminding clients about safe sex methods available to them and providing a conduit for additional support. Upon enrollment into the study, participants in all groups will receive a face-to-face baseline behavioral survey conducted by a data collection team who remained masked to intervention allocation at enrollment.

The baseline questionnaire (see Additional file 5) was designed by the study team using sections from standard questionnaires currently in use at KHANA for assessing similar measures in populations of high-risk women in Cambodia. The questionnaire was created in English, translated to Khmer, and back-translated to English. The questionnaire will be pilot tested with 15 FEWs similar in eligibility to future study participants using cognitive interviewing techniques [48]. Next, participants will be randomized into intervention and control groups: Group 0 is the control group and Group 1.1 and 1.2 are the intervention group (1.1 = SMS [1.1a Khmer characters or 1.1b Romanized Khmer] or 1.2 = VM in Khmer).

Those in the control group will get one “check-in” SMS or VM between baseline and midline and another between midline and endline. Participants will be asked to confirm receipt of this message. These messages will contain no health information and will be used as a way to stay in touch with participants and to compare “receipt confirmation” rates to the intervention group. All participants will be asked to choose whether they would prefer to receive SMS or VM and their reason for their choice. If they choose SMS, they will be asked if they prefer Khmer characters or Romanized Khmer. Recent studies on choosing the method for receiving interventions during an RCT have demonstrated that it may increase participation and retention [49].

A message schema was developed in which each participant will receive a message from a different topic group each week for 10 weeks. The messages will tend to follow a flow of rights-based health information and then linkage (though there is some variance depending on topic). However, after each message, participants will also have the option to be linked to an outreach worker. After the tenth week, the topic areas will cycle through again, but the messages within the topic areas will be unique. After weeks 30, 40, and 50 (+ 2), messages will be repeated to reinforce particular concepts and ideas. Participants who indicate they would like to talk to a counselor will receive a call from a *Mobile Link* staff. The counselor will provide individualized information via telephone or face-to-face on that particular topic and, if needed, can escort the participant to receive the required services.

Participants will also receive a weekly 5–7-question survey that asks about more common and/or time-sensitive issues such as STI symptoms, vaginal infection/irritation, support for GBV, or psychological issues. Once a month, participants will be asked if they are using contraception and/or want to be linked to family planning counseling. Participants who endorse any of the survey questions will be asked if they want to be linked to an outreach worker. Therefore, it is important to note that, while the topics in the messages will change each week—as well as the topical prompts for linkages to outreach workers—the weekly monitoring survey provides another consistent and constant platform for mobile linkage.

Trained data collectors and community health workers in the selected sites will deliver the *Mobile Link* intervention. SMS/VM are scheduled and sent using the open-source software program developed by InSTEDD (instedd.org). InSTEDD and the Project Coordinator will retain data on the SMS/VM messages sent, responses to messages, and outcomes of follow-up phone calls.

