#### Control group

Participants in the control group will receive the current existing standard of care, but not the health-related SMS/VMs or associated follow-up phone calls. Standard of care consists of access to existing HIV and SRH services which includes: face-to-face counseling; free HIV and STI testing and condoms; and clinic phone numbers and hotline phone numbers with a toll-free help line for clients staffed by trained counselors. Control group members will receive “check-in” reminder calls before questionnaire appointments (midline and endpoint).

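### The planned between-arm comparison of receipt confirmation is not like for like, and the sections on check-ins and survey reminders need to be reconciled

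*Protocol article*

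**What the plan says.** Under Phase II: Intervention, the protocol article gives each control participant one check-in "SMS or VM between baseline and midline and another between midline and endline". It adds that "Participants will be asked to confirm receipt of this message". It then gives the purpose: "These messages will contain no health information and will be used as a way to stay in touch with participants", and also to set their confirmation rates against those of the intervention group.

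The same section describes what intervention women receive: weekly topic messages with health content and an offer of contact with an outreach worker, and a weekly survey of five to seven questions. It describes no check-in and no request to confirm receipt for them. It does say that messages sent and responses to them are retained, and Additional analyses plans to describe responses to voice messages and weekly surveys.

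Three sections bear on contact before the surveys:

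- Phase II: Intervention makes the control check-in an SMS or voice message sent between surveys.
- Control group uses the same term for "reminder calls before questionnaire appointments (midline and endpoint".
- Baseline data collection states that "All participants will receive SMS/VM appointment reminders for the surveys", and gives one procedure for tracing missed visits without distinction by arm.

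The Abstract (Methods) also says that controls receive a weekly monitoring survey. The Control group section does not mention one.

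**The concern.** A receipt-confirmation comparison is useful if it shows whether the two arms are equally reachable. For that, both arms must be asked to do the same thing. Acknowledging a neutral message is a different task from replying to a health message or completing a short survey. A difference in rates could reflect reachability, interest in the content or effort of replying, and the planned data could not separate these. Equal rates would be no easier to interpret.

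The reminder wording matters for a different reason. If one arm received an additional call just before the outcome surveys, attendance could differ by arm. Analyses of primary and secondary outcomes counts women lost to follow-up at six months as non-users. Under that rule an attendance difference becomes an outcome difference, even with no true effect. The Discussion already expects difficulty with follow-up, so retention procedures deserve exact wording.

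**Working it through.** The plan states no rate, power or sample size for this comparison, so there is no figure to reproduce. The check is a reading of the sections against each other, with short illustrations whose assumptions are marked.

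**1. Prompts per arm.** Study design gives a "12-month RCT with two arms of 300 FEWs each". Control check-ins are 2 per woman, so 300 × 2 = 600. For the intervention arm the article supports three counts:

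- one topic message a week (Phase II): about 52 per woman, 300 × 52 = 15,600;
- the eligibility criterion "be willing to receive two SMS/VM per week for one year": 2 × 52 = 104 per woman, 300 × 104 = 31,200;
- the six messages in the adherence definition (Sensitivity and per-protocol analyses): 300 × 6 = 1,800.

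**2. If the rate is scored per woman as ever confirmed.** Let p be the chance of confirming any one message, assumed equal in both arms and independent between messages, and m the number of messages. Then P(at least one) = 1 − (1 − p)^m.

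| Assumed p | m = 2 (control) | m = 6 | m = 52 |
|---|---|---|---|
| 0.1 | 19% | 47% | 99.6% |
| 0.3 | 51% | 88% | about 100% |
| 0.5 | 75% | 98% | about 100% |
| 0.7 | 91% | 99.9% | about 100% |

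For example, at p = 0.3: 1 − 0.7² = 0.51 and 1 − 0.7⁶ = 0.88. Reachability is identical by construction, so the gap comes from message count alone.

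**3. If the rate is scored per message.** With the same p in both arms, both rates equal p and the count artefact disappears. The rates still refer to different stimuli: neutral check-ins in one arm, health messages or surveys in the other. If content or task changes p, that change cannot be told apart from a difference in reachability.

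**4. Reminders side by side.** Baseline data collection gives all women message reminders and the same tracing. Control group names a call before the midline and endpoint questionnaires, and no counterpart call is described for the intervention arm. Adding the two sections gives controls the common reminder plus a call. However, Control group describes what controls receive and does not say that others receive no call. It also reuses the term check-in, so it may be a loose restatement of the Phase II message.

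**5. What an attendance difference would do.** Background reports that 52.3% of FEWs had an HIV test in the past six months. Assume that control attendance at six months rises by 5 percentage points and that the extra attenders test at that rate. The control proportion counted as tested then rises by 0.05 × 52.3% = 2.6 points. The direction is against the intervention. The 5 points are an assumption; nothing in the document estimates them.

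**The case against.** The article is a condensed account. It speaks of a rate in the intervention group, which implies that one will be defined, and it says that responses to messages are logged. The unit and denominator may well be in the full protocol. A light, neutral contact for controls is also a reasonable choice when the other arm is messaged every week. These points stand, and they rule out saying that the intervention arm has no measure at all. They do not make the comparison like for like: the article itself fixes who gets the check-in and what it is for, and the logged responses are to other kinds of message.

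Three stronger readings are tempting, and the document supports none of them.

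- A reader might infer that survey reminders differ by arm. Baseline data collection gives reminders and tracing to everyone, and Control group does not restrict its call to controls. This is a wording conflict, not an established difference.
- A reader might set 104 contacts against 2 and report a 52-to-1 imbalance. That picks one of three message counts in the article and ignores the Abstract, which gives controls a weekly survey. It distorts the result only under a per-woman scoring that the article does not state.
- A reader might infer that the call unblinds the data collectors. The Control group section does not say who places it.

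**Conclusion.** The point holds at low severity. As described, the announced comparison sets confirmations of a neutral check-in in controls against responses to health messages and surveys in the intervention arm. It therefore cannot isolate reachability. A per-message rate removes the effect of message count but not that of content and task; a per-woman rate removes neither.

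The descriptions of the check-in in Phase II: Intervention and Control group do not agree, and neither fits cleanly with the common reminders in Baseline data collection. An additional control call is the literal reading but is not certain. Its effect on the outcomes is therefore a possibility, of the order of 2.6 points for each assumed 5 points of attendance.

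Severity stays low because receipt confirmation is neither a primary nor a secondary outcome, and message responses are planned as descriptive process data. No efficacy conclusion depends on the receipt comparison.

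**What to change.** 1. Send the identical content-free check-in, with the same request to confirm receipt, to both arms at the same two times. Base the receipt comparison on these messages only, as confirmations divided by check-ins sent.
2. State one survey-reminder procedure for both arms: same mode, timing and number of attempts, preferably carried out by staff who do not conduct the interviews.
3. Reconcile Baseline data collection, Phase II: Intervention and Control group on what the check-in is and who receives which reminder. Reconcile the Abstract with the Control group section on whether controls receive the weekly survey.

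The cost is 2 × 300 = 600 extra automated messages and some rewording. Trial status says recruitment had not started, so the change could be made before any data were collected. With 600 check-ins per arm, an assumed rate of 50% and an assumed within-woman correlation of 0.2 to 0.8, the 95% half-width in each arm is about 4.4 to 5.4 points (1.96 × √(0.25 × (1 + correlation) / 600)), before allowing for venue clustering. That is adequate for a descriptive process measure.

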### Primary outcomes

All outcomes will be self-reported and collected through surveys. The primary outcome measures will include: (1) HIV testing; (2) condom use at last sex; (3) frequency of condom use (always, sometime, rarely, never) with clients; (4) frequency of condom use (always, sometime, rarely, never) with boyfriends; (5) STI screening when experiencing symptoms; (6) STI treatment when diagnosed; (7) contraceptive use; (8) unwanted pregnancy and unsafe abortion; and (9) experiences with GBV.

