### Risks to human participants

#### Human participant involvement, characteristics, and design

The focus of this study is to increase the rates of HIV testing and condom use in FEWs because they have been identified as a group that is at-risk for HIV infection. Female young adults who are classified as a vulnerable population comprise most of the study population. Because this study is testing an intervention tailored specifically to females, men will not be eligible to be participants. All recruitment activities and study procedures involving study participants will follow national guidelines. We anticipate involving a minimum of 600 FEWs in the study, and our sampling strategy will ensure that the group of participants is representative of the total population of young FEWs in Cambodia. Assigning study arms will be done at random, meaning that all participants have an equal chance of being assigned into the two active arms or the control arm. They will not be masked to the intervention since the intervention involves receiving SMS/VMs on their mobile phones.

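### Data collectors are named both as blinded interviewers at six and 12 months and as staff who deliver Mobile Link, so interviewer blinding at follow-up is contradicted as written

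*Protocol article*

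**What the plan says.** Study design describes a "multisite, single-blind, 12-month RCT with two arms of 300 FEWs each". The section on human participant involvement says of the participants: "They will not be masked to the intervention since the intervention involves receiving SMS/VMs on their mobile phones". The label must therefore refer to someone other than the women enrolled.

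Baseline data collection says who that is: "Data collectors, who will be blinded to the trial arm assignment, will collect baseline data from participants recruited". The same sentence extends their task to follow-up, where they act "as well as survey them at six and 12 months". Sampling and participant recruitment agrees on who conducts the follow-up: "a six-month and 12-month questionnaire will be administered by trained data collectors".

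Phase II: Intervention then assigns delivery: "Trained data collectors and community health workers in the selected sites will deliver the" Mobile Link intervention. The Control group section withholds the health messages and the calls that follow from them from controls.

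Under Primary outcomes: "All outcomes will be self-reported and collected through surveys".

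**The concern.** One named staff group holds two roles that cannot be combined in the same person without losing the blinding. Someone who helps deliver messages, calls or linkage to one arm knows that a woman is in that arm.

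The blinding matters more than usual here because little else protects measurement. The women know their allocation. The primary outcomes include condom use with clients and boyfriends, STI screening and treatment, unsafe abortion and gender-based violence, all of which are open to socially desirable answers. A woman interviewed by someone she associates with the programme may answer more favourably, and an interviewer who knows the arm may probe or record differently. Either would act in one arm only and would look like a treatment effect. The five effect measures in the cost-effectiveness analysis are also self-reports from the baseline and follow-up surveys, so any distortion would carry into the incremental ratio.

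**Working it through.** The article gives no figure on this point, so the check is a comparison of its statements about roles.

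1. **Who is blinded.** Participants are not (human participant involvement section). Data collectors are (Baseline data collection). Sampling and participant recruitment also says allocation is concealed from the researchers, because the statistician receives only ID numbers and venue type. That does not reach field staff who deliver to one arm. The blinding that protects outcome measurement is that of the interviewers.

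2. **When it has to hold.** Both Sampling and participant recruitment and Phase II place the baseline survey before randomisation, so interviewers cannot know the arm then. Only the six- and 12-month surveys are at issue. Baseline data collection claims blinding for those, and Sampling and participant recruitment gives them to the same staff group.

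3. **Who delivers.** Phase II names trained data collectors together with community health workers, and does not limit the data collectors' share.

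4. **Whether delivering reveals the arm.** The Abstract gives the weekly monitoring survey to controls as well, so handling that survey need not reveal the arm. The health messages and associated calls do, because the Control group section withholds them from controls.

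5. **Whether the article separates two teams.** It does not. The term data collectors is used without distinction under Sampling and participant recruitment, Baseline data collection and Phase II.

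6. **Whether an objective endpoint limits the damage.** Primary outcomes makes every outcome self-reported. Analyses of primary and secondary outcomes mentions an objective measurement of contraceptive use, but only as a check on self-report and without defining it.

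Steps 2 to 5 give the result: the same named group is blinded at follow-up and delivers something that reveals the arm, and no text reconciles the two.

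**The case against.** The strongest reply is that the delivery sentence is loose wording in a condensed article. Phase II says the messages are automated and sent by software. It gives calls to Mobile Link staff or a counsellor, and linkage to outreach workers. Sampling and participant recruitment describes the program coordinator as the person delivering the intervention. The planned process interviews cover community health workers and outreach workers, not data collectors. No section gives data collectors a specific task that would reveal the arm. Two separate teams of data collectors would satisfy every sentence.

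Much of this stands. A reader might infer that blinding is certain to fail, and the documents do not support that. They show a contradiction, not a known staffing arrangement. But the article states no separation, and the delivery sentence is unqualified.

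Three further inferences should be resisted.

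- **Masking that lapses after enrolment.** Phase II describes a survey "conducted by a data collection team who remained masked to intervention allocation at enrollment". That refers to the baseline survey and does not narrow the follow-up claim under Baseline data collection.
- **One woman's arm revealing that of her whole venue.** Sampling and participant recruitment allocates venues within pairs, but Phase II and the human participant involvement section speak of participants being randomised. The unit of allocation is itself inconsistent, so this point should not rest on it.
- **All reporting bias coming from interviewers.** Unmasked women can report differently by arm to a perfectly blinded interviewer. Blinding the interviewer is partial protection.

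**Conclusion.** The point holds as a contradiction in the current text. Interviewer blinding at six and 12 months is claimed in one section and undercut in another, in a trial where participants are unmasked and all outcomes are self-reported. It needs correcting because differential reporting, once present in the data, could not be separated from the intervention effect by the planned models.

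Its size is unknown. A reader might assume an over-report of some points in the intervention arm and convert it to a false-positive rate with a two-proportion test at 300 per arm. The documents do not support such a figure. They give no basis for the assumed bias, which would determine the answer. The calculation would ignore clustering by venue and the planned group-by-time test by generalised estimating equations. It would also charge to interviewers a bias that unmasked participants could produce alone.

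The conclusion rests on reading data collectors as one group wherever the term appears. If two teams are intended, the defect is in the text only, and one sentence cures it.

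**What to change.** Reconcile Study design, Baseline data collection and Phase II: Intervention in one of these ways.

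- Remove data collectors from the delivery sentence. Community health workers, outreach workers and counsellors are already named in the plan for this work.
- Or state that those who conduct the six- and 12-month surveys are a separate team with no delivery role and no access to the allocation list or the messaging platform.
- If neither is feasible, withdraw the single-blind claim and state the risk of reporting bias as a limitation.

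Under either of the first two, add one item that the interviewer completes after each follow-up survey, recording whether she or he learned the participant's arm. Participants may disclose it, and the record would show how far the blinding held.

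The cost is small: a change of wording, one form item and somewhat less flexible rostering at the sites. Trial status says recruitment has not started, so roles can be fixed before any outcome is collected.
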